**Fig. 3 Fig3:**
[figure not shown]
Study inclusion and exclusion criteria

#### Exclusion criteria

Women where a pathogenic variant in a moderate or high risk gene has been identified as the cause of cancers in the family will be excluded from the study, as will men, who constitute a very small proportion of index cases (<5%) and relatives (<10%). Men will be excluded from the study as the small sample size will preclude a meaningful statistical comparison with the majority female cohort. Women who receive an intermediate PRS will also be ineligible, because intermediate PRS results do not alter a woman’s risk status and hence risk management advice in a clinically meaningful way. Patients with obvious intellectual or mental impairment that may interfere with the patient’s ability to understand the requirements of the study will also be excluded. Women who are not sufficiently proficient in English to be able to provide written informed consent and complete questionnaires in English will not be recruited to the study.

#### Recruitment

Women selected for inclusion will be invited participate in the psychosocial study by letter. The invitation package will also include a participant information and consent sheet, a response form and a two-page educational pamphlet on genomic testing and breast cancer risk. The educational pamphlet has already been developed and has been pilot-tested with ViP participants to facilitate an informed decision about whether to attend an FCC to receive one’s polygenic risk result (unpublished data).

#### Measures

Women will complete the three self-administered questionnaires over a 12-month period (see Additional file 1). A summary of the measures included at each time point is shown in Table 1.

**Table 1 Tab1:** Measures selected for study and corresponding questionnaires

Measure	Q1 Baseline	Q2 Receivers	Q3 Receivers	Q3 Decliners
Predictor Variables				
1. Demographic characteristics	√			
2. Protection motivation	√			
3. Perceived severity of breast cancer	√			
4. Response efficacy	√			
5. Response cost	√			
6. Self-efficacy	√			
7. Uncertainty avoidance	√			
Confounding Variable				
8. Stressful life events	√		√	√
Predictor and Outcome Variables				
9. Perceived breast cancer risk	√	√	√	
10. Knowledge of familial breast cancer and polygenic risk	√	√	√	
11. Breast cancer anxiety	√	√	√	√
Outcome Variables				
12. General anxiety and depression	√	√	√	√
13. Concordance with screening guidelines	√		√	√
14. Intention to take up and actual uptake of preventative strategies	√	√	√	√
15. Regret over testing decision		√	√	√
16. Recall and interpretation of results		√	√	
17. Test-related distress, positive experiences and uncertainty		√	√	
18. Reasons for declining results				√

Clinical data available through the ViP study includes: number of affected first- and second-degree relatives, including number deceased due to breast cancer, personal history of breast cancer, and for affected women, time since diagnosis.

#### Predictor variables

*Demographic characteristics –* sociodemographic data to be collected includes age, gender, country of origin, marital status, educational level, income, language spoken at home, number of biological children, and previous attendance at an FCC.
*Protection motivation –* one 7-point Likert-type item will assess intention to receive PRS result.
*Perceived severity of breast cancer* – will be assessed with one item adapted from a previous study [35].
*Response efficacy –* six items were adapted from [35] to assess perceived benefits of receiving one’s PRS. Participants will be asked to rate from ‘not at all’ (1) to ‘very much’ (3) the extent to which different factors have influenced their decision to access their PRS result (e.g. learn about my children’s risk, to plan for the future).
*Response cost –* six items were adapted from [35] to assess perceived disadvantages to receiving a PRS result. Participants will be asked to rate from ‘not at all’ (1) to ‘very much’ (3) the extent to which different factors have influenced their decision not to access their result (e.g. concern about the impact of genetic information on my family, possible impact on insurance).
*Self-efficacy –* will be measured with seven items to assess confidence in undertaking SNP testing despite ‘obstacles’. Participants will be asked to rate their agreement from ‘strongly disagree’ (1) to ‘strongly agree’ (5) with statements such as ‘I am confident I can receive my genomic testing result even if’…‘my family did not want me to, I had to communicate the results to my family’ [34].
*Uncertainty avoidance* – will be assessed using the eight-item Attitudes Towards Uncertainty scale [36], which has previously demonstrated high internal reliability [34]. The eight items are measured on a five-point scale ranging from ‘strongly disagree’ (1) to ‘strongly agree’ (5), with higher scores indicating a more negative attitude towards uncertainty.

#### Confounding variable

8.
*Stressful life events*: will be assessed using the 12-item List of Threatening Experiences, which measures common threatening life experiences, including serious illness and death in the family [37]. Threatening life events may affect anxiety and distress levels and will be measured as potential confounding variable.

#### Predictor and outcome variables

9.
*Perceived breast cancer risk* – will be measured with three items used in a previous study [35].10.
*Knowledge of familial breast cancer and polygenic risk* – 10 true-false items have been developed to assess knowledge of polygenic inheritance and hereditary breast cancer.11.
*Breast cancer anxiety:* will be measured using the Impact of Events Scale (IES), a measure of intrusion and avoidance toward a stressor, in this case being at risk for breast cancer [38]. The IES consists of 15 items with response options ranging from ‘not at all’ (0) to ‘often’ (5). A total score is obtained by summing the items (range 0 to 75) with a higher score indicating more distress [38]. The IES has been validated in similar populations [39].

#### Outcome variables

12.
*General anxiety and depression:* will be assessed using the Hospital Anxiety and Depression Scale (HADS). The 14-item HADS is a widely used measure of emotional disturbance and has two subscales measuring general anxiety and depression [40]. Each question has four possible responses, with responses scored on a scale from 0 to 3. A total scale score is obtained by summing each item (range 0 to 42) with a higher score indicating more general anxiety and depression.13.
*Concordance with screening guidelines* – six items have been developed in concordance with national guidelines for mammography and clinical breast examination [41] screening using the approach used in a previous study [42]. Participants will be categorized in terms of their concordance to the current screening guidelines.14.
*Intention to take up and actual uptake of preventative strategies –* 15 items have been developed to assess intention and uptake of preventative strategies, including risk-reducing surgery (bilateral mastectomy), medication (i.e. tamoxifen and raloxifen), and lifestyle factors (i.e. alcohol consumption, and exercise).15.
*Regret over testing decision* – will be assessed using the five-item Decision Regret Scale, which correlates with decisional conflict and quality of life [43].16.
*Recall and interpretation of testing results* – three items have been developed to assess recall and understanding of testing results.17.
*Test-related distress, positive experiences and uncertainty –* this measure includes 19 items from a validated questionnaire, the Multidimensional Impact of Risk Assessment Scale [44], assessing distress (six items), positive experiences (four items), and uncertainty (nine items) about genetic testing. Response options range from ‘never’ (0) to ‘often’ (5) with higher scores indicating higher psychological distress.18.
*Reasons for declining results* – will be assessed with 15 items used in a previous study [18]. Women will be asked to indicate the extent to which possible reasons for declining to receive results apply to them.

#### Genetic counseling consultation and disclosure of results

In line with clinical care practice, participants will receive their PRS result by attending an in-person appointment with a qualified genetic health professional (genetic counselor and/or medical geneticists) at one of the participating FCCs. As the return of polygenic information represents a novel practice in genetic counselling, genetic health professionals at each of the participating FCC will receive training on polygenic inheritance. A training manual will also be developed covering: interpretation of PRS results and current research, genetic counseling frameworks for polygenic inheritance [27, 31, 45, 46], impact on risk management options, implications for family members, and potential psychosocial implications.

To measure consultation characteristics, a brief consultation report will be completed after each appointment which includes: participant’s PRS result, type of cancer (for affected women), recommended risk management strategies, number of occasions of service, length of consultation, and health professionals involved in the consultation.

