**Methods:**

In this prospective study, 400 women with a personal and/or high risk family history of breast cancer will be recruited from six familial cancer centers (FCCs) in Australia. Eligible women will be invited to attend a FCC and receive their personal polygenic risk result for breast cancer. Genetic health professionals participating in the study will receive training on the return of polygenic risk information and a training manual and visual aids will be developed to facilitate patient communication. Participants will complete up to three self-administered questionnaires over a 12-months period to assess the short-and long-term psychological and behavioral outcomes of receiving or not receiving their personal polygenic risk result.

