To date there has been little research on the uptake and effective communication of this complex polygenic information in the hereditary cancer setting. Early research has been primarily based on hypothetical scenarios assessing interest and attitudes towards testing for common risk variants. These studies have reported a strong interest in polygenic risk testing with interest ranging from 74% to 78% [26–30]. Similarly to uptake of *BRCA1*/2 testing, interest was more consistently related to psychological factors (i.e. perceived risk and greater cancer worry), rather than sociodemographic variables [26–30]. Only two studies have assessed actual uptake of testing and associated outcomes [31, 32]. These studies offered testing for common risk variants associated with colorectal cancer risk; however, they were limited by the small number of variants tested and hence the associated cancer risk was uncertain. The authors concluded that the behavioral changes observed (improvement in diet and exercise) were a result of the genetic counselling, which emphasized lifestyle factors associated with colorectal cancer risk, rather than a result of the polygenic risk information.

Despite increasing support for the utility of common risk variants in hereditary breast cancer [8–12], research has not yet been integrated into clinical practice. Testing for polygenic risk in breast cancer is not currently available in any clinical setting, or currently considered for return to patients outside of a research setting by any FCCs in Australia or internationally. This reflects the status of polygenic risk as an emerging technology and the limited amount of information available on the outcomes of offering such testing. Translational research is needed to develop a model of genetic counselling for polygenic breast cancer risk, which addresses the psychosocial needs of patients and assists health professionals in communicating these complex results to patients.

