### Common genomic variants and familial cancer cohort

The Common Genomic Variants and Familial Cancer Study (commonly known as: the Variants in Practice study, ViP) provides a unique cohort in which to systematically ascertain the important psychosocial and clinical implications of testing for polygenic risk and answer a large number of research questions at a small cost [9]. The cohort consists of over 4400 men and women from Victoria and Tasmania, Australia, who have a high-risk family history of breast cancer. Prior to enrolment in the study, all index cases will have attended a participating FCC and undergone clinical assessment, including molecular testing of *BRCA1/2* and other genes depending on their family history and phenotype. Unlike index cases, only a small proportion of family members have a personal history of cancer and most have not attended a FCC. To date 3700 of the total study cohort have had genomic testing for 96 SNPs already known to be associated with breast cancer risk.

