### Study design

Assessing a woman’s breast cancer risk by profiling common risk variants represents a novel approach in clinical genetics. The PRS results referred to in the protocol are research results obtained from the ViP study and will only be available to the 400 women invited to participate in this psychosocial study.

This is a prospective study which is being conducted across FCCs in two Australian states (Victoria and Tasmania). The study has been approved by the Peter MacCallum Cancer Centre Ethics Committee (HREC/16/PMCC/2) and the Tasmanian Health and Medical Human Research Ethics Committee (H0016395).

The primary psychological outcome measurement is breast cancer anxiety as assessed by the Impact Event Scale (IES). The secondary psychological and behavioral outcomes are: i) general anxiety and depression, ii) test-related distress, positive experiences and uncertainty, iii) concordance with screening guidelines, iv) uptake of preventative strategies, and v) level of decisional regret. The method of determining the PRS has been described elsewhere [9].

Data will be collected through self-reported questionnaires. Over the course of the study, participants will complete up to three questionnaires. Women who choose to receive their PRS result will complete three questionnaires: at baseline (prior to attending the FCC), two weeks after receiving their PRS result, and 12 months after receiving their result. Women who choose not to receive their result will complete two questionnaires: at baseline and 12 months after enrolment in the study (Fig. 2).

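### The 12-month receiver–decliner comparison combines the choice to receive, the clinic consultation and the result, so it cannot be read as the effect of receiving polygenic information

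*Protocol article*

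**What the plan says.** All statements are from the protocol article.

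- **Receivers.** Under Genetic counseling consultation and disclosure of results, "participants will receive their PRS result by attending an in-person appointment with a qualified genetic health professional". A report completed after each appointment covers, among other items, "recommended risk management strategies, number of occasions of service, length of consultation".
- **Decliners.** Study design: "Women who choose not to receive their result will complete two questionnaires: at baseline and 12 months after enrolment in the study". No appointment is described for them.
- **Everyone invited.** Recruitment: "The invitation package will also include a participant information and consent sheet, a response form and a two-page educational pamphlet on genomic testing".
- **Earlier clinic contact.** In the parent cohort, "all index cases will have attended a participating FCC and undergone clinical assessment" at a familial cancer clinic (FCC) before enrolment. Among relatives, "only a small proportion of family members have a personal history of cancer and most have not attended a FCC".
- **Use of the contrast.** Hypothesis 1a(ii) predicts better compliance with screening guidelines at 12 months in receivers than in decliners. Aim 2 also covers behavioral outcomes of both groups. Statistical analyses plans regressions comparing them, with age, parity and stressful life events as example adjusters.
- **Wording of the purpose.** The abstract says that the questionnaires assess the "psychological and behavioral outcomes of receiving or not receiving their personal polygenic risk result". The Discussion opens by describing the study as one of the impact of receiving this information.
- **Limitations.** Two are listed: English-only questionnaires and the absence of pre-test counselling.

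**The concern.** Receivers and decliners differ in three ways at once: receivers chose to have the result, sat with a genetics professional who recommended risk management, and learned their polygenic risk score (PRS). A higher screening rate among them at 12 months could come from any of the three.

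The protocol has met a related problem. Its Background reports that authors of the only two studies of actual polygenic testing concluded that the behavioral changes they saw "were a result of the genetic counselling, which emphasized lifestyle factors associated with colorectal cancer risk, rather than a result of the polygenic risk information".

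The study is meant to support a new service model. If a receiver–decliner difference were reported as a behavioral effect of PRS information, it would credit the score with something that a consultation based on family history, or the motivation of the women who came, might produce without it.

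**Working it through.** **Step 1. What each group has.**

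| Component | Receivers | Decliners | Section |
|---|---|---|---|
| Pamphlet with the invitation | yes | yes | Recruitment |
| Earlier FCC care, index cases | yes | yes | Common genomic variants and familial cancer cohort |
| Earlier FCC care, relatives | most in the parent cohort had none; not given by group | same | same |
| Chose to have the result | yes | no | Study design |
| Study consultation with recommendations | yes | none described | Genetic counseling consultation and disclosure of results |
| PRS result | yes | no | same |

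The first three rows do not separate the groups by design. The last three do.

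**Step 2. What the contrast estimates.** In a simple additive sketch, let s be the difference due to self-selection, c the effect of the consultation and r the effect of the result. Then

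receiver − decliner difference = s + c + r.

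That is one equation with three unknowns. Baseline covariates can remove part of s. They cannot remove c, because no decliner is described as having the consultation: an indicator for it would be the receiver indicator itself.

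**Step 3. Why c need not be zero.** For relatives who had not attended an FCC, the disclosure appointment may be the first specialist discussion of familial risk. The Background says that families with uninformative genetic tests already receive risk assessment and screening advice based on family history. Advice can therefore change screening without a PRS.

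**Step 4. Size.** The protocol gives no figure for this contrast. Its sample-size arithmetic is consistent (215 + 105 = 320; 320 / (1 − 0.20) = 400), but the 80% power is claimed for hypothesis 2c, which lies within receivers. The documents give neither the index/relative split of the 400 women nor any consultation effect.

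The following is illustration only, on assumed inputs:

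- If a share f of receivers attend for the first time and a first consultation raises concordance by g, the spurious gap is f × g. With f = 0.3 and g = 10 points it is 3 points; with f = 0.6 and g = 20 points it is 12 points.
- Suppose r = 0 and s = 0, and the consultation raises concordance by Δ averaged over all receivers. With 105 decliners and 215 receivers at two-sided 5%, the chance of a significant difference is Φ[(Δ − 1.96·SE₀)/SE₁], with SE₀ pooled and SE₁ unpooled. For 50% v 60%: pooled rate (52.5 + 129)/320 = 0.567; SE₀ = 0.0590; SE₁ = √(0.25/105 + 0.24/215) = 0.0591; Φ[(0.10 − 0.1156)/0.0591] = 0.396.
- Over decliner rates of 50%, 60% and 70%, this chance is 13–16% for Δ = 5 points, 40–51% for 10 points and 73–87% for 15 points.

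So a modest consultation effect might or might not show up. The documents do not say where in this range the study lies.

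**Step 5. The comparison within receivers.** High minus low PRS among receivers holds choice and attendance constant, so those terms cancel. What remains is the result plus the advice attached to it. The Background gives different advice by PRS group, so these two still move together. Hypothesis 2a(ii) sets this contrast for risk-reducing strategies; no hypothesis sets it explicitly for screening. Table 1 collects screening concordance at Q1 and Q3 in both groups, and previous FCC attendance is among the baseline items.

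**The case against.** The strongest reply is that the protocol never says the receiver–decliner contrast isolates information from counselling. Hypothesis 1a(ii) stands under Aim 1, on uptake and its correlates. The goal is a service in which results are returned in clinic, so consultation plus result is the package of interest.

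Part of this stands: as an association with the package, the contrast is legitimate. But screening 12 months after the result comes after the uptake decision and cannot be a determinant of it. Aim 2 also treats the groups' outcomes as outcomes, and the abstract and Discussion attribute them to receiving the information. For a clinic deciding whether to add a PRS, the natural comparator is a consultation without one.

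Four stronger readings are tempting, and the documents do not support them:

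- *Decliners get nothing.* They get the pamphlet, and index cases among them have had FCC care. The flow figure is not shown, and their usual care is not addressed.
- *The study repeats the earlier studies' confounding.* Those studies concerned diet and exercise after colorectal counselling that stressed lifestyle. They show that the issue was known, not that it will recur for breast screening.
- *The study cannot address the effect of the result.* Hypotheses 2a to 2c, including the powered one, lie within receivers.
- *High versus low PRS isolates the information.* It holds attendance constant but not advice.

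It can also be said that subgroup analyses belong in an analysis plan. That is fair for their detail. The mismatch between the contrast and the wording of its purpose is in the article itself.

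**Conclusion.** The point holds for the 12-month receiver–decliner contrasts, mainly hypothesis 1a(ii). They estimate an association with choice, consultation and result together, and the wording in the abstract and Discussion goes further than that. The omission from the limitations is real.

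No size can be derived. A reader might take the 3 to 12 points above as an estimate of bias, but both inputs are assumed. The conclusion rests on one reading of the text: that decliners have no study consultation, since none is described. It does not depend on the assumed figures and leaves the within-receiver hypotheses untouched.

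**What to change.** 1. State that 1a(ii) and the other 12-month receiver–decliner contrasts are associations with the whole package in self-selected women, and add this to the limitations. Align the wording in the abstract and Discussion.
2. Adjust the 12-month screening contrast for Q1 screening concordance, and present it separately for women with and without previous FCC attendance.
3. Add 12-month screening behavior, adjusted for Q1, to the high versus low PRS contrast among receivers. Because advice differs with the score, measure screening against one yardstick common to all receivers as well as against the advice in each woman's consultation report. Say that this contrast holds attendance constant while result and result-specific advice still move together.

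No new data are needed. The costs are a narrower receiver–decliner claim, two further pre-planned analyses, and lower precision in the smaller attendance subgroups.
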